# Evaluating the effects of increasing physical activity to optimize rehabilitation outcomes in hospitalized older adults (MOVE Trial): study protocol for a randomized controlled trial

**DOI:** 10.1186/s13063-014-0531-y

**Published:** 2015-01-15

**Keywords:** mobility limitation, rehabilitation, exercise therapy, hospitalization, randomized controlled trial

## Abstract

**Background:**

Older adults who have received inpatient rehabilitation often have significant mobility disability at discharge. Physical activity levels in rehabilitation are also low. It is hypothesized that providing increased physical activity to older people receiving hospital-based rehabilitation will lead to better mobility outcomes at discharge.

**Methods/Design:**

A single blind, parallel-group, multisite randomized controlled trial with blinded assessment of outcome and intention-to-treat analysis. The cost effectiveness of the intervention will also be examined. Older people (age >60 years) undergoing inpatient rehabilitation to improve mobility will be recruited from geriatric rehabilitation units at two Australian hospitals. A computer-generated blocked stratified randomization sequence will be used to assign 198 participants in a 1:1 ratio to either an ‘enhanced physical activity’ (intervention) group or a ‘usual care plus’ (control) group for the duration of their inpatient stay. Participants will receive usual care and either spend time each week performing additional physical activities such as standing or walking (intervention group) or performing an equal amount of social activities that have minimal impact on mobility such as card and board games (control group). Self-selected gait speed will be measured using a 6-meter walk test at discharge (primary outcome) and 6 months follow-up (secondary outcome). The study is powered to detect a 0.1 m/sec increase in self-selected gait speed in the intervention group at discharge. Additional measures of mobility (Timed Up and Go, De Morton Mobility Index), function (Functional Independence Measure) and quality of life will be obtained as secondary outcomes at discharge and tertiary outcomes at 6 months follow-up. The trial commenced recruitment on 28 January 2014.

**Discussion:**

This study will evaluate the efficacy and cost effectiveness of increasing physical activity in older people during inpatient rehabilitation. These results will assist in the development of evidenced-based rehabilitation programs for this population.

**Trial registration:**

Australian New Zealand Clinical Trials Registry ACTRN12613000884707 (Date of registration 08 August 2013); ClinicalTrials.gov Identifier NCT01910740 (Date of registration 22 July 2013).

## Background

The aging population represents a significant and growing challenge to the Australian [1], US [2] and other healthcare systems [3]. In Australia in 2011 and 2012, people aged over 65 years accounted for 48% of all hospital bed days and 39% of hospital discharges [4], despite only representing 14.4% of the population [1]. Older people often require inpatient mobility rehabilitation after discharge from an acute hospital to enable them ‘to reach and maintain their optimal physical, sensory, intellectual, psychological and social functional levels’ [5]. In turn, this can help them to return to previous living arrangements and lifestyle.

Mobility outcomes following rehabilitation are often poor in older adults. Many older people are frail and have impaired mobility on admission to an inpatient geriatric rehabilitation unit, and evidence indicates that mobility outcomes remain suboptimal in many older people following discharge from these facilities [6,7]. For example, a recent study found that 14% of older people discharged from an inpatient geriatric rehabilitation unit were unable to walk 10 meters [6]. Of those who could walk 10 meters, only 31% were independent when walking up stairs. Gait speed was also reduced, with a very low median speed of 0.46 m/sec (IQR = 0.32), compared to a mean speed of 1.2 to 1.3 m/sec in healthy older adults [6]. Mobility problems commonly persist following discharge, with only 41% of older adults being able to walk 800 meters or climb a flight of stairs 3 months after discharge [7]. Poor mobility can have serious consequences for older adults. It is associated with the need for long-term care [8], loss of functional independence and mortality [9] and falls [10]. It is therefore important to maximize recovery of mobility in older people with mobility disability.

While it is widely believed that bed rest and inactivity in hospital are detrimental for mobility and function [11], there are no definitive clinical guidelines on optimum physical activity levels for older adults undergoing inpatient rehabilitation. Despite the publication of physical activity guidelines for older people [12-15], a gap exists in guidelines for frail older people or those who have multiple chronic diseases and are undergoing rehabilitation. A number of studies indicate that activity levels in rehabilitation are low [16-18] and that physical activity levels in aged care rehabilitation are particularly low [19]. This raises the possibility that better outcomes could be achieved by adding interventions, strategies and systems to increase physical activity. Increasing physical activity is a simple intervention likely to have a positive impact on recovery of mobility.

Surprisingly, there is limited research examining the effect of increasing physical activity on mobility outcomes in hospitalized older people undergoing rehabilitation. These patients typically have a wide variety of admission diagnoses and multiple co-morbidities, which may include cognitive impairment [6]. As a consequence, they are often excluded from clinical trials. A recent systematic review [20] found providing hospitalized patients with an additional average of 19 minutes physiotherapy per day led to improvements in mobility and quality of life and reductions in length of stay. However, the average age of participants in the review was only 69.8 years. There is some evidence that a multidisciplinary exercise intervention in an acute hospital reduces acute length of stay and increases the proportion of older people who return home [21]. There is also promising evidence that increasing physical activity in a range of outpatient, home and residential care settings can improve outcomes in some older people [22-24]. A pilot study conducted by our group demonstrated the feasibility of utilizing a randomized controlled trial (RCT) to examine the impact of increased physical activity on mobility outcomes in older people receiving inpatient geriatric rehabilitation. A satisfactory recruitment and retention rate was achieved, protocols to increase physical activity were developed, increases in physical activity were obtainable, there was no evidence of group contamination, and there was no increase in adverse events [25]. Given the success of the pilot trial and the potential for mobility improvements via increasing physical activity, a larger and appropriately powered RCT to further explore the efficacy of increasing physical activity in older people on mobility and other outcomes is warranted.

The proposed study will test the primary hypothesis that increasing physical activity in older people during rehabilitation, compared with a control group, will lead to better mobility at discharge, as measured by self-selected gait speed. Secondary hypotheses follow concerning the increase of physical activity during rehabilitation:It will lead to significantly greater improvements in secondary measures of mobility and function both at discharge and 6 months after discharge.It will lead to a better quality of life 6 months after hospital discharge.It will be cost effective compared to usual care.

## Methods/Design

### Design

An investigator and assessor-blinded, parallel group multisite RCT will be used to compare enhanced physical activity to ‘usual care plus’ provided to older people receiving in-hospital geriatric rehabilitation at hospitals in the Melbourne metropolitan area of Victoria, Australia. Figure 1 provides an overview of the study design. Reporting of results will conform to the recommendations of the Consolidated Standards of Reporting Trials (CONSORT) statement [26]. Ethical approval has been obtained from the La Trobe University Human Ethics Committee (12-122), and from ethics committees at each site prior to commencement at that site (Austin Health Human Research Ethics Committee approval H2013/05042, Monash Health Human Research Ethics Committee approval14117X). The trial has also been registered with The University of Melbourne (Ethics ID 1340834) and Curtin University (HR 25/2014). Any protocol amendments will be submitted to the relevant Ethics Committees for review and will be updated on the trial registries.

**Figure 1 Fig1:**
[figure not shown]
**Participant flow-through study.** TUG, Timed up and go; DEMMI, De Morton Mobility Index; FIM, Functional Independence Measure; EQ5D, Euro QoL Health Questionnaire; EQ-VAS, Euro QoL, Visual Analog Scale.

### Participants

Older people will be recruited within 48 hours of admission to rehabilitation and geriatric evaluation and management wards of the participating hospitals. People admitted to these wards are medically stable, but may have chronic or complex health conditions that require treatment and management by a multidisciplinary team, or require a period of rehabilitation to maximize function. A member of the research team will screen each person upon admission and approach potential participants in person. To be included in the study, participants must be aged 60 years or older and have a goal of admission to ‘improve mobility or improve walking’ as determined by admission referral or the treating therapist. Participants will be excluded if (1) there are specific medical restrictions that limit mobilization, (2) mobility goals are limited to non-weight bearing mobility goals, (3) they are already enrolled in an RCT, or (4) the primary reason for admission is to await residential care or carer training. Informed consent will be obtained from the participant, or ‘responsible person’ if the participant is unable to give consent due to cognitive impairment. Interpreters will enable recruitment of people who are non-English speaking.

### Randomization

As study site and mobility on admission are potential confounders, randomization will be blocked and stratified by site and mobility level. At baseline, the mobility of participants will be classified as either non-ambulant (Level 1 or 2 as detailed in Table 1) or ambulant (Level 3 or 4 as detailed in Table 1)*.* This classification will be used for stratification by mobility level. Once consent has been obtained and baseline data collected, participants will be individually randomized to an intervention group (enhanced physical activity) or a control group (usual care plus) according to a computer generated randomization procedure performed by a third party. Group assignment will only be available to intervention staff and the project manager, and will be accessed online via a password protected site.

**Table 1 Tab1:** **Functional classification of participants and summary of activities for intervention group**

**Level**	**Function**	**Intervention**
1	Patient is unable to transfer out of bed without maximum assistance (two persons or a hoist) and has poor static and dynamic sitting balance (unable to sit independently).	Bed exercise program (including lower limb, upper limb and abdominal strength and bed mobility) and sitting balance exercises.
2	Patient can transfer out of bed with assistance from one person, has independent sitting balance, but is unable to stand independently. Requires moderate assistance from two people to walk.	Sitting exercise program including targeted lower limb strengthening exercises. Sit to stand exercises, standing balance exercises, stepping/marching on the spot as able (using rails/ gait aids for safety as indicated). Activities from the previous level may be included if specifically indicated. For example, if the participant is unable to perform full range movement against the effects of gravity, specific lower limb muscle strengthening exercises may be performed on the bed.
3	Patient can walk with minimal assistance from one person.	Walking exercises, sit to stand exercises, standing balance exercises, and step up exercises. Targeted lower limb strength exercises (where possible closed chain or functional strengthening exercises).
4	Supervision only or independence with ambulation. Requires minimal assistance or supervision on stairs.	Stairs exercises, walking exercises (including outdoor mobility), step up exercises, standing balance exercises. Targeted lower limb strength exercises as indicated (where possible closed chain or functional strengthening exercises).

Reprinted from Said, C. M., Morris, M. E., Woodward, M., Churilov, L., & Bernhardt, J. (2012). Mobility in older adults receiving hospital based rehabilitation: A phase II feasibility study. BMC Geriatrics, 12:26. doi: 10.1186/1471-2318-12-26.

### Outcome measures

#### Primary outcome

The primary outcome measure is mobility on discharge from hospital as assessed using gait speed. This will be measured using the 6-meter walk test [27] at self-selected speed by a trained assessor blinded to group allocation. Participants will be instructed to walk at self-selected speed along a 10-meter walkway, and a stopwatch will be used to measure speed over the middle 6 meters. Participants will be allowed to use a gait-aid if required, and this will be recorded. Up to three trials will be performed, and the best performance recorded. Participants unable to complete the test will be given a score of 0 m/sec. Gait speed was chosen as a primary outcome measure as it is associated with the need for long-term care [8], functional dependence, mortality [9] and falls [10]. Gait speed can also predict activity levels at home and in the community [28,29] and increases in gait speed are associated with improvements in overall health status [30]. Furthermore, gait speed has good retest reliability [27,31] and is responsive to changes in walking ability [32-34].

#### Secondary outcomes

Secondary outcome measures include mobility on discharge from hospital as assessed using the Timed Up and Go (TUG) [31,35] and the De Morton Mobility Index (DEMMI) [36-38]. Gait speed will also be measured 6 months postdischarge as a secondary outcome measure. Additional secondary outcomes include function, as measured using the Functional Independence Measure (FIM^TM^) [39], health-related quality of life, as measured by the EuroQol health questionnaire (EQ5D) and the EuroQol Visual Analog Scale (EQ-VAS) [40] and subacute length of stay (LOS). These tests will be administered in accordance with previously published protocols. If a participant is unable to complete the EQ5D or EQ-VAS due to cognitive impairment, a proxy will complete it on their behalf.

#### Tertiary outcomes

Tertiary outcomes of mobility, function and quality of life will be obtained 6 months postdischarge, using the TUG [31,35], the DEMMI [36-38], the FIM [39], the EQ5D and the EQ-VAS.

Falls will be monitored throughout the study. Falls will be defined as ‘an unexpected event in which you come to rest on the ground, floor or lower level’ [41]. Data on falls during the period of hospitalization will be obtained via review of medical records and hospital incident reports. Falls in the 6 months postdischarge will be recorded prospectively via a monthly falls calendar provided to participants at discharge. Participants will be asked to record the date of any falls and whether or not advice or treatment from a health professional had been sought related to the fall. They will be asked to return the calendar at the end of each month, and will receive a telephone reminder if the falls calendar is not returned. This method of falls data collection is considered the ‘gold standard’ for collecting falls data [41].

### Assessments

Each assessment will be completed at three time points by an assessor blinded to group allocation. All assessors will be trained to ensure the assessments are standardized and will be FIM^TM^ credentialed.

#### Baseline

The baseline assessment will be completed within 48 hours of admission. In addition to primary and secondary outcome measures collected at baseline, additional demographic and clinical data will be obtained. These data will include the participant’s age, sex, height and weight, acute LOS, mental state (measured by the Mini Mental State Examination [42]), frailty (measured using the modified Fried Frailty Index) [43,44], co-morbidities (age adjusted Charlson Comorbidity Score [45]), depression (Geriatric Depression Scale [46]), medications, self (or carer) reported falls in the last 12 months and social situation.

#### Discharge

The second assessment will be completed within 48 hours of discharge. Self-selected gait speed (primary outcome) at this assessment will be the primary endpoint of the study. In addition to the primary and secondary outcome assessments, discharge destination and service referrals on discharge will also be collected. For participants discharged to residential care, the day the treating team determined that they required residential care placement and required paperwork was completed will be used in lieu of actual discharge date for this analysis.

#### Six months postdischarge

The third and final assessment will be conducted 6 months postdischarge in the person’s residence. In addition to further secondary and tertiary outcome assessments, falls data and any associated health professional advice or treatment will be collected.

### Interventions

Both the intervention and control group will be provided with usual care, which will include ongoing therapy provided by a multidisciplinary team including nurses, medical staff, physiotherapists, occupational therapists and other allied health professionals as required throughout their in-patient rehabilitation. Both groups will receive additional therapy sessions, but the content of these sessions will differ depending on group allocation.

#### Intervention group: enhanced physical activity

In addition to usual care, participants in the enhanced physical activity intervention group will undertake 1 to 2 sessions of additional physical activities on weekdays, and a further two sessions each weekend throughout their inpatient stay (anticipated average of 19 days, based on data from the participating hospitals). Programs will be individually tailored with the aim of increasing the amount of time participants spent performing mobility exercises, such as standing or walking. Intervention protocol guides, which were trialed in the pilot study, [25] will be specified for participants according to their functional level (summary provided in Table 1; full details provided in trial manual available from authors). Specific targets for activity levels on weekdays and weekends have been set, based on pilot data [19,25]. All sessions will be provided by a physiotherapist or physiotherapy assistant not involved in the provision of usual care to participants. At the end of each intervention session, the physiotherapist or allied health assistant will record the amount of time spent performing each activity in 5-minute increments. No specific program to be completed outside of these sessions will be provided.

#### Control group

To control for the extra hours of social interaction received by participants in the enhanced physical activity group, participants in the control group will undertake additional seated or resting social activities including card and board games, conversation and reading, as well as upper limb and other physical exercises that have minimal impact on mobility. These sessions will be provided by either a physiotherapist or physiotherapy assistant, and time involved in these sessions will be recorded.

### Risk management and safety monitoring

There is a risk that the intervention may result in an increase in adverse events, although no differences between groups were reported in the pilot study [25]. In the event of a fall or medical event, standard hospital procedures will be followed. Falls during hospital stay, mortality and unplanned re-admissions to an acute service (during rehabilitation or within six months postdischarge) will be recorded on an incident form, monitored by an independent Data Safety and Monitoring Committee and reported to the relevant ethics committees.

### Data management

All data will be stored in a confidential manner. Participants will be assigned a code, which will be used for all data management and analyses. Paper data will be stored at the local site in a locked filing cabinet. Coded electronic data will be stored on a computer server at The Florey Institute of Neuroscience and Mental Health for the duration of the study. Access to the computer files will be password-protected and accessible only to the research team. Data quality will be monitored by the project manager on a regular basis and reported to the management committee. The project manager will also conduct regular site visits to monitor trial conduct. All project investigators will have access to the final, de-identified data set.

### Sample size estimation

The sample size for this study was calculated based on pilot data, which showed that the median gait speed of people discharged from aged care rehabilitation was 0.46 m/sec (range 0.1 to 1.2 m/sec) [6], which allowed a mean gait speed (0.46 m/sec) and variance (0.18 m/sec) to be estimated [50]. Sample size estimation was based on the intervention group achieving an increase in gait speed of at least 0.1 m/sec compared with the control group, the recommended minimal clinically important difference for gait speed in older adults [30,51]. With a two-tailed significance threshold alpha of 0.05 and power to yield a statistically significant result set at 90%, a sample size of 69 participants in each group is required. To account for an estimated 25% dropout rate and 14% of participants being unable to complete the walk test on discharge, as observed in pilot data [6,25], an estimated 198 participants will be required in total [52]. A recruitment rate of 34% was achieved in the pilot study. Based on average hospital admissions to the selected sites in this trial, and using a conservative recruitment rate of 20%, it is anticipated that the recruitment will be completed over 13 months.

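### The planning spread of 0.18 m/sec is an SD mislabelled as a variance and fits poorly with the IQR of 0.32 quoted from the same source, so the stated 90% power is unsupported

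*Protocol article*

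**What the plan says.** The section Sample size estimation cites an earlier cohort (reference 6): "median gait speed of people discharged from aged care rehabilitation was 0.46 m/sec (range 0.1 to 1.2 m/sec) [6". From these summaries it takes its planning values, "which allowed a mean gait speed (0.46 m/sec) and variance (0.18 m/sec) to be estimated". The target is the "intervention group achieving an increase in gait speed of at least 0.1 m/sec compared with the control group", and the error rates are given as "With a two-tailed significance threshold alpha of 0.05 and power to yield a statistically significant result set at 90" percent. The result is that "a sample size of 69 participants in each group is required", raised to 198 in total for 25% dropout and for 14% unable to complete the walk test.

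The Background cites reference 6 for the same median but gives another measure of spread: "with a very low median speed of 0.46 m/sec (IQR = 0.32" m/sec). The sample size section does not use that IQR.

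The abstract states without qualification: "The study is powered to detect a 0.1 m/sec increase in self-selected gait speed in the intervention group at discharge". The primary analysis is an ANCOVA on baseline gait speed, by intention to treat with imputation, and a participant who cannot complete the walk test scores 0 m/sec.

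**The concern.** Two things look wrong. First, a variance of gait speed cannot have the unit m/sec, so either the label or the number is off. Second, the protocol quotes two measures of spread from one cohort, range and IQR, and sizes the trial on the one that yields the smaller SD. Sample size grows with the square of the SD, so 0.24 in place of 0.18 matters.

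At stake is the power claim for the trial's one confirmatory comparison, at a difference that the protocol itself calls the minimal clinically important one.

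**Working it through.** **Inputs from the protocol.** Difference d = 0.1 m/sec; two-sided alpha 0.05; power 90%; spread 0.18; 69 per group; median 0.46; range 0.1 to 1.2; IQR 0.32; 14% unable to complete the test; 25% dropout; 198 randomized 1:1, so 99 per group.

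**1. Reproduce the stated number.** n per group = 2 × [(1.960 + 1.282) × SD / d]².
- 0.18 as an SD: 2 × (3.242 × 1.8)² = 68.1, rounded up to 69. The t-test power at 69 per group is 90.0%. This matches.
- 0.18 as a true variance: SD = √0.18 = 0.424, and n = 379. This does not match.

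So 0.18 was used as an SD.

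**2. Where 0.18 may come from.** Range/6 = (1.2 − 0.1)/6 = 0.183. The protocol does not spell out the formula, so this is a match and not a proof.

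**3. Compare with the IQR.**
- A normal distribution with SD 0.18 has IQR 1.349 × 0.18 = 0.243, against 0.32 quoted.
- An IQR of 0.32 gives SD = 0.32/1.349 = 0.237 under normality.
- The quoted range looks right-skewed: 0.36 below the median and 0.74 above. With median 0.46 and IQR 0.32, a gamma shape gives SD 0.248 and a lognormal 0.282.
- A uniform distribution with IQR 0.32 has width 0.64 and SD 0.64/√12 = 0.185, yet the observed range is 1.1.

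**4. Power on the protocol's own unadjusted basis, SD 0.237.**
- 69 per group: 69.1% (t-test) or 69.7% (normal approximation).
- n for 90%: 119 per group (normal) or 120 (t-test).
- Difference detectable with 90% power at 69 per group: 3.242 × 0.237 × √(2/69) = 0.13 m/sec.

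**5. Effect of the planned ANCOVA.** Residual SD = 0.237 × √(1 − r²), where r is the baseline-discharge correlation. The documents give no r, so the values are assumptions.

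| r | Residual SD | Power, 69 per group |
|---|---|---|
| 0 | 0.237 | 69% |
| 0.5 | 0.205 | 81% |
| 0.6 | 0.190 | 87% |
| 0.7 | 0.169 | 93% |

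The r at which the residual SD returns to 0.18 is √(1 − (0.18/0.237)²) = 0.65.

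**6. Numbers analysed.** Non-completers score 0 and stay in, so 25% dropout leaves 99 × 0.75 = 74 per group. Unadjusted power at SD 0.237 is then 72%. With all 99 analysed, and no information lost to imputation, it is 84%.

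**7. The endpoint with zeros.** The cohort's range starts at 0.1 and the Background reports the 14% who could not walk separately, so the IQR appears to describe walkers. Assume 14% zeros, and walkers with mean 0.46 and SD 0.237:

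variance = 0.86 × 0.237² + 0.86 × 0.14 × 0.46² = 0.0484 + 0.0255 = 0.0739, so SD is about 0.27.

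For a full 0.1 m/sec difference in the overall mean, unadjusted power is about 57% at 69 per group and 73% at 99.

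**The case against.** The best defence has three parts.

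*An IQR does not determine an SD.* This is true, and it rules out calling the two figures a strict contradiction, which a reader might infer. The value 0.237 depends on approximate normality. What stands is a poor fit: an SD near 0.18 needs a middle about as flat as a uniform distribution together with the long observed tails, and the skewed shapes tried push the SD up.

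*69% is not the power of the planned trial.* This is also true. A reader might take the trial to have 69% power in place of 90%, but the documents do not support that. The primary analysis adjusts for baseline and uses all randomized participants; with a correlation of 0.7, power at 69 per group is 93%. Sizing a trial without adjustment ahead of an ANCOVA is an ordinary conservative choice. But the protocol takes no credit for adjustment and states no correlation, so this shows that 90% may be reached, not that it has been justified. Larger analysed numbers help, while scoring non-completers as 0 pulls the other way.

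*The harm is limited.* A reader might infer that a null result would be over-read as excluding a 0.1 m/sec effect. Nothing in the protocol says so: whether that difference is excluded depends on the confidence interval observed, not on planned power. Type I error and the validity of the comparison are unaffected.

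**Conclusion.** The point holds as a mislabelled and probably optimistic SD behind an unsupported power statement. On the protocol's own unadjusted basis, the IQR that it quotes takes power at 69 per group from 90% to about 69%, assuming approximate normality, and lower under the skewed shapes tried. Whether the planned analysis reaches 90% is open: at SD 0.237 and 69 per group it needs a correlation of about 0.65 or more. The SD of about 0.27 for the endpoint with zeros rests on the further assumptions of 14% zeros and a walker mean of 0.46, and would make the requirement stricter. The label error is certain; that 0.18 is too small is very likely; the exact replacement value cannot be settled without the cohort data.

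**What to change.** In Sample size estimation:

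1. Relabel 0.18 m/sec as a standard deviation.
2. Replace it with the SD from the group's own cohort data, computed for the endpoint as defined with non-completers scored 0. If the raw data are not available, use the IQR-based value of about 0.24 for walkers and show about 0.27 with zeros, stating the assumptions.
3. Keep 198 participants and restate power as a range: unadjusted, and under ANCOVA for stated baseline-discharge correlations. At SD 0.237 and 69 per group this reads 69% unadjusted, and 81%, 87% and 93% at 0.5, 0.6 and 0.7. Give the matching figures for the SD finally adopted.

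In the abstract, amend the statement that the study is powered for a 0.1 m/sec increase so that it agrees with the restated range.

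The cost is a rewritten paragraph, one short calculation and a less favourable power statement. No extra participants are needed, and neither the primary analysis nor trial conduct changes.

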## Trial status

The trial commenced recruitment on 28 January 2014 and is currently open for recruitment. Recruitment will cease when 198 participants have been randomized. It is anticipated this target will be reached by April 2015.

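### On the protocol's own loss assumptions, 198 randomised leave about 128 evaluable rather than the required 138, so power is about 88% (unadjusted), not 90%

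*Protocol article*

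**What the plan says.** All inputs are in the Sample size estimation section of the protocol article. The target is "the intervention group achieving an increase in gait speed of at least 0.1 m/sec compared with the control group". The spread comes from pilot data, "which allowed a mean gait speed (0.46 m/sec) and variance (0.18 m/sec) to be estimated". The error rate and power follow: "With a two-tailed significance threshold alpha of 0.05" and "power to yield a statistically significant result set at 90" per cent. This gives 69 per group.

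The section then inflates: "To account for an estimated 25% dropout rate and 14% of participants being unable to complete the walk test on discharge", and concludes that "an estimated 198 participants will be required in total". No inflation formula is shown; a reference is cited. The abstract repeats the number with equal allocation ("assign 198 participants in a 1:1 ratio"), and Trial status makes it the end of enrolment: "Recruitment will cease when 198 participants have been randomized".

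Two other sections bear on what counts as a loss. Under Primary outcome, a participant who cannot do the walk test is scored 0 m/sec. Under Statistical analysis, the primary analysis takes in all randomised participants. Deaths count as zero, transfers to acute care go to an adjudication panel, and other missing values are multiply imputed.

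**The concern.** Inflation for loss should leave the required number after the loss has occurred. With a loss fraction d, that means dividing by (1 - d). Multiplying by (1 + d) always gives too little: adding 25% to 69 gives 86.25, and losing 25% of that leaves 64.7, not 69. The step from 69 per group to 198 in total looks like the multiplying version.

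What is at stake is the power stated for the primary endpoint. Because 198 is also where recruitment stops, an inflation error carries straight through to the number enrolled.

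**Working it through.** **Inputs** (Sample size estimation): difference 0.1 m/sec; spread 0.18 m/sec; two-sided alpha 0.05; power 90%; equal allocation; losses of 25% and 14%. The 0.18 is called a variance but carries the units of an SD, and only as an SD does it reproduce 69. A variance of 0.18 would need 379 per group. It is used as an SD below.

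**1. Reproduce 69.** n per group = 2 x (1.960 + 1.282)² x 0.18² / 0.1² = 68.09, rounded up to 69. A two-sample t-test with 69 per group has power 0.900. The base figure is correct.

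**2. Reproduce 198.**
- 69 x 1.25 x 1.14 = 98.3, rounded up to 99 per group, 198 in total.
- A second route also arrives there: 68.09 / 0.86 x 1.25 = 98.97, again 99 per group. It divides for the 14% and multiplies only for dropout.
- Dividing for both: 69 / (0.75 x 0.86) = 106.98, rounded up to 107 per group, 214 in total.

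So 198 is consistent with multiplication, certainly not with division for both losses, and the exact route cannot be settled from the article. Both routes that reach 198 multiply for dropout.

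**3. What 198 delivers if both percentages are losses.** This step does not depend on which formula was used.
- Evaluable: 198 x 0.75 x 0.86 = 127.7, or 63.9 per group.
- Shortfall: 138 - 127.7 = 10.3 evaluable participants.
- Power at 63.9 per group, SD 0.18, no covariate: 0.876 (t-test) or 0.881 (normal approximation), about 88%.
- Number needed to retain 138: 138 / 0.645 = 213.95, so 214, which is 16 more than 198.
- For 198 to retain 138, total loss would have to be 1 - 138/198 = 30.3%. The sequential loss is 1 - 0.645 = 35.5%. The smaller figure would need an overlap between the two groups that the article does not state.

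**4. What 198 delivers if non-completers are scored 0 and analysed.** Only the 25% is then lost.
- Head count: 198 x 0.75 = 148.5, above 138. Enrolling 138 / 0.75 = 184 would be enough for the count.
- The SD of 0.18 no longer applies. It was derived from gait speeds with a minimum of 0.1 m/sec, so it contains no zeros. Zeros raise the SD and shrink the mean difference.
- Illustration, on assumptions that are not in the article: 14% zeros in both groups, walkers' means 0.46 and 0.56, walkers' SD 0.18. The difference becomes 0.86 x 0.1 = 0.086. The group variances are 0.86 x (0.18² + 0.46²) - (0.86 x 0.46)² = 0.0533 and 0.86 x (0.18² + 0.56²) - (0.86 x 0.56)² = 0.0656, a pooled SD of 0.244. With 74.25 per group, power is about 57% before baseline adjustment.
- With a baseline correlation r, the SD becomes 0.244 x sqrt(1 - r²). Power is then about 69% at r = 0.5 and 85% at r = 0.7. No value of r is given.

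**The case against.** The strongest objection is that the 14% are not lost at all. They receive a score of 0 m/sec and enter an analysis of everyone randomised, and part of the 25% will also have a value through the rules for deaths, acute transfers and imputation. This stands as far as the head count goes: on that reading 198 is more than enough to retain 138. It does not confirm 198 as derived. The sample size section itself adds participants to make up for the 14%, and if that factor is dropped, the SD and difference behind the 69 no longer describe the outcome being analysed. Multiple imputation does not replace lost participants one for one, and the calculation takes no credit for it.

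The second objection is that the primary analysis is an ANCOVA on baseline gait speed, while the 88% is for an unadjusted comparison. This also stands. Taking the residual SD as 0.18 x sqrt(1 - r²), 64 per group regain 90% at r of about 0.28 and reach about 95% at r = 0.5. The article states no correlation and claims no such gain, so this could justify 198 but is not how 198 was justified.

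Third, the formula is inferred. That is so, and for this reason the finding rests on the 127.7, which needs no assumption about the formula.

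A reader might go further and add the two percentages into one 39% loss among all randomised, which would make the shortfall larger. The documents do not support that. The Background reports the 14% among people discharged from a rehabilitation unit, so it applies to those who reach discharge, and the sequential 0.75 x 0.86 is the version that fits.

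**Conclusion.** The point holds in a limited form. Taking the sample size section at its word, with 25% and then 14% lost, SD 0.18 and no covariate, 198 gives about 128 evaluable participants (64 per group) and about 88% power. The stated 90% would need 214. The shortfall is about 10 evaluable participants and 2 points of power. It does not threaten the trial.

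A reader might infer that the trial will fail to reach 90% power whatever is done. The documents do not support that: a modest baseline correlation would restore it in the situation of step 3. Nor do they support the statement that the authors certainly multiplied by 1.25 and 1.14.

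The larger uncertainty is that the loss assumption and the planned handling of non-completers disagree. Under the planned handling, the 14% changes the SD and the mean difference rather than the count, and the article gives no power for that analysis. The 57% above shows the direction under stated assumptions and is not an estimate for this trial. Whether 0.18 is a fair SD among walkers is a separate question and is not used here.

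**What to change.** Keep 198 and correct the sentence in Sample size estimation:

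- State that, with 25% dropout and 14% non-completion both treated as losses, 198 leave about 128 evaluable and give about 88% power in an unadjusted comparison with SD 0.18. Add that this is before any gain from the baseline covariate, and give the correlation if one is to be relied on. Print the inflation formula.
- In the same place, reconcile this with Primary outcome and Statistical analysis. If non-completers are scored 0 and analysed, drop the 14% loss factor, note that 198 then leave about 148, and recompute power with an SD and mean difference that include the zeros.

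Printing only 214, or only 88%, would leave a figure for an analysis that the rest of the article does not plan.

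The cost is a sentence or two and one further power calculation, which needs an assumed proportion of zeros per group and, if used, a baseline correlation. The correction of the inflation step does not by itself call for more enrolment.
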